### Outcome measures and data collection

The primary outcome measure (for phases 3 and 4) is (change in) the NOM rate. Type of treatment (NOM vs operative treatment) will be extracted from the DHFA. The DHFA is a national database, including over 95% of Hip fracture patients and can provide automated anonymous patient data up to 1 year after hip fracture treatment. To evaluate the effect of the implementation, the change in NOM rate and operative rate for the targeted population will be evaluated and compared with the rate prior to implementation. This will be calculated using the annual national DHFA data from the 2 years preceding implementation per hospital, as baseline. The postimplementation NOM rate will be collected immediately after completion of phase 4, as well as at the end of 2025. The secondary outcome measures (for phase 3 only) will be collected during semistructured interviews with patients/proxy or next-of-kin, 4–6 weeks after inclusion. These are the satisfaction with the chosen treatment on a numeric rating scale (0–10), their valuation of the information received during the SDM process, and if the patient’s needs were respected enough in the treatment decision. The interview sheets (in Dutch), used for patient or healthcare provider interviews in phases 1–3, are included in online supplemental materials 2.

10.1136/bmjopen-2023-083429.supp2Supplementary data

The following patient data will be also collected in phases 3 and 4 from the DHFA at 3 months and 1 year after hip fracture treatment (emerging from the patients’ medical records). Patient characteristics (age, sex, ASA, FAC), prefracture situation (residence, mobility, Katz Activities of Daily Living (ADL) score), fracture details (fracture classification, affected side), hospital details (hospital length of stay and intensive care length of stay) and outcome details (complications, revision surgeries, readmission, 30-day mortality and time until death).

Data will be collected for each patient who meets the eligibility criteria. To reduce the administrative burden, the DHFA database will be used as much as possible. Data from the DHFA will be imported in a Castor EDC database, in which hospitals can only see their own data. The datasets of all hospitals will be combined for the final analysis.

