### Statistical analysis

Data will be analysed by using the SPSS V.28 or higher (SPSS). Normality of continuous data will be tested with the Shapiro-Wilk test, and homogeneity of variances will be tested using the Levene’s test. A p<0.05 will be taken as threshold of statistical significance. Missing values will not be imputed.

The primary outcome, NOM rate, will be determined by dividing the number of patients treated with NOM by the total eligible number of patients (per participating centre and for all participating centres combined).

All continuous data will be reported as mean with standard deviation (SD; if normally distributed based on Shapiro-Wilk test) or as median with quartiles (if not normally distributed). Categorical data will be reported as number with percentage. Preimplementation and postimplementation data will be compared with a Student’s t-test (continuous data, normally distributed), Mann-Whitney U-test (continuous data, non-normally distributed), or a χ^2^ or Fisher’s exact test (categorical data), as applicable. The analysis will be stratified by NOM versus operative treatment, and further stratified as feasible depending on the final study population, for example, by time since NOM implementation, prefracture mobility, ADL status, fracture classification or bilateral fracture.

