## Discussion

### Clinical impact

This project provides an important translation of recent scientific publications to clinical practice and its success could play an important role in (inter)national surgical and geriatric guideline changes. Successful implementation of NOM will change the way healthcare providers view acute hip fractures in frail older adults with a limited life expectancy. Instead of primarily focusing on clinical possibility of hip fracture treatment, the focus will shift towards treatment concerning patients’ quality of life, harm reduction and effective palliative care in the final stages of life. Because of this shift, the NOM rate is expected to rise in this select group. However, the main goal is not to increase NOM rate but to provide each patient with the clinical care that best suits their wishes, needs and clinical reality. Nationwide implementation of SDM on NOM will also lead to a reduction of overtreatment and might reduce associated costs.^10^ Another important outcome is reduced practice variation between hospitals in both patient selection for (SDM on) NOM and nationwide implementation of a universal structured SDM protocol for frail older adults with a hip fracture.

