### Strengths and limitations

The strength of this study is that it builds on an existing foundation of recent well-received (inter)national publications, countrywide initiatives involving SDM and advance care planning, and recent demands for assistance in the implementation of NOM from several hospitals. The project group includes experienced professionals from (orthopaedic) trauma surgery, geriatrics, epidemiology and implementation science from both university medical centres and general hospitals, supplemented with patient perspectives and experts in SDM and study methodology. A limitation of the project is the limited time period for the initial project. Achieving nationwide implementation within 2 years, which is the maximum allowed project duration of the grantor, might be an overoptimistic aim. However, the project will have developed a strong foundation on which future projects can build and will keep sharing its tools and information, even after completion. Another limitation is that the inclusion criteria might prove to be too narrow. There might be a larger group of patients for whom NOM could suit their preferences or goals of care. However, the project group has decided to keep strict criteria to prevent the pendulum swinging too far and causing undertreatment with long-term survival without functional recovery after opting for non-operative treatment, which results in potential decreased quality of life and associated adverse events. Depending on the results of the initial implementation, the inclusion criteria in the protocol might be adjusted to suit the needs of patients and healthcare providers. Finally, the NOM rate in the DHFA database might be an underestimation, as patients living in a nursing home might already have advance care plans preventing them from being transferred to the hospital in the case of a hip fracture. As the NOM implementation gains national traction more attention to advance care planning around hip fractures might lead to an unmeasured increase of the NOM rate in the prehospital setting. While reducing DHFA registration for this project, improved communication on patients wishes and integration of hip fractures in advance care planning, between patients and (geriatric) medical practitioners within and outside the hospital, is a desired effect that will improve the quality of NOM and patients’ treatment satisfaction.

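### Before-after tests within NOM and operative strata condition on the treatment choice the implementation is meant to change, so both strata can appear to improve when outcomes among all eligible patients have not

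*Protocol article*

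**What the plan says.** All references are to the protocol article.

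- **Primary outcome** (Outcome measures and data collection): "The primary outcome measure (for phases 3 and 4) is (change in) the NOM rate". Under Statistical analysis it is obtained by "dividing the number of patients treated with NOM by the total eligible number of patients".
- **Other data** (Outcome measures and data collection): the audit also supplies hospital and intensive care length of stay and "complications, revision surgeries, readmission, 30-day mortality and time until death". These are listed as additional data. The named secondary outcomes are the interview measures of phase 3.
- **Tests** (Statistical analysis): the threshold is p<0.05, and "Preimplementation and postimplementation data will be compared with a Student’s t-test", or with a Mann-Whitney, chi-squared or Fisher test as the data require.
- **Stratification** (next sentence of the same section): "The analysis will be stratified by NOM versus operative treatment". This is unconditional. Only the further strata, such as prefracture mobility or fracture classification, depend on feasibility.
- **Expected direction** (Clinical impact): "the NOM rate is expected to rise in this select group".

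**The concern.** The stratifying variable is determined after the implementation has acted, and it is the variable the implementation acts on. When more patients choose NOM, some who would formerly have been operated on change stratum. If they tend to be sicker than those still operated on but fitter than the earlier NOM patients, their move lowers mortality in both strata without altering any patient's risk. This is stage migration.

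Two conditions are needed: the NOM rate must move, and treatment choice must be related to prognosis. The protocol expects the first. The second is plausible, since the target group is defined by limited life expectancy and the Introduction reports higher mortality with NOM. The documents do not quantify it, however, and part of that mortality difference could be an effect of treatment.

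At stake is a report, in a project that hopes to inform guidelines, that outcomes improved after implementation among both NOM and operated patients when the eligible population fared the same or worse.

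**Working it through.** **1. Size figure in the plan.** Sample size calculation: 25% x 17,225 = 4,306, which reproduces the stated figure of about 4,300 per year. About half meet the criteria: 4,306 / 2 = 2,153, say 2,150 eligible per year. The plan gives no NOM rate, stratum mortality or power.

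**2. The mechanism by counting (invented figures).** Take 1,000 eligible patients in each period: 100 always choose NOM (80% die), 100 move from operation to NOM (50% die either way), and 800 are always operated on (15% die).
- NOM stratum: before 80/100 = 80%; after (80 + 50)/200 = 65%.
- Operated stratum: before (50 + 120)/900 = 18.9%; after 120/800 = 15%.
- All eligible: (80 + 50 + 120)/1,000 = 25% in both periods.

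**3. A range.** Assumptions, none given by the documents:
- Prognosis Z is standard normal and P(death) = expit(-1 + Z). Overall mortality is then 30.3%, close to the Introduction's 1-year figure of over 30%.
- Neither treatment nor implementation affects death.
- NOM is chosen when a normal score with correlation rho to Z exceeds the cut-off that gives NOM rate q, and q goes from 10% to 30%.

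NOM mortality is E[P(death) x P(NOM given Z)] / q. Operated mortality is (overall - q x NOM mortality) / (1 - q). Differences below are from unrounded values.

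| rho | NOM stratum | Operated stratum | All eligible |
|---|---|---|---|
| 0 | 30.3% to 30.3% (0) | 30.3% to 30.3% (0) | 30.3% to 30.3% |
| 0.3 | 40.2% to 36.7% (-3.5) | 29.2% to 27.6% (-1.6) | 30.3% to 30.3% |
| 0.5 | 47.4% to 41.1% (-6.3) | 28.4% to 25.7% (-2.7) | 30.3% to 30.3% |
| 0.7 | 55.0% to 45.8% (-9.2) | 27.6% to 23.7% (-3.9) | 30.3% to 30.3% |
| 0.82 | 59.8% to 48.7% (-11.0) | 27.1% to 22.4% (-4.6) | 30.3% to 30.3% |

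If q stays at 10%, every difference is zero.

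**4. Sensitivity to the model.** A probit risk model with overall mortality 30% and the same rise in NOM gives -5.0 and -2.3 points at rho 0.3, -8.9 and -3.8 at 0.5, and -12.9 and -5.5 at 0.7.

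**5. Chance of p<0.05 with no true change.** Assume national data, two baseline years (2 x 2,150 = 4,300 eligible), one year after (2,150), and a two-sided two-proportion test in each stratum. For 10% to 30% at rho 0.5, the chance is about 52% per stratum in the model of step 3 and about 81% in the probit model. For a weak case (rho 0.3, 10% to 20%) it is about 9% and 14%. The nominal rate is 5%.

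**6. Masking.** In the model of step 3, add 0.25 to every patient's log-odds of death after implementation. True mortality rises from 30.3% to 34.9%.
- At rho 0.82 both strata still fall: NOM 59.8% to 54.3%, operated 27.1% to 26.6%.
- At rho 0.5, NOM falls from 47.4% to 46.4% and operated rises only from 28.4% to 30.0%.
- At rho 0.3 both rise, by 1.5 and 2.8 points, less than the true 4.6.

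**The case against.** **The primary analysis is sound.** This stands. A reader might infer that stratifying by treatment empties the primary outcome, since the NOM rate within NOM is 100% and within operation 0%. The text does not support that reading: the NOM rate has its own paragraph and is taken over all eligible patients.

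**Stratified need not mean only stratified.** The test sentence carries no restriction to a stratum, so an unstratified comparison is not excluded, and case-mix adjustment may be set out in an analysis plan that is not shown. This stands as far as it goes, and the point does not rest on the absence of adjustment. It rests on a stated rule that places before-after tests inside treatment strata.

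**The affected variables are supporting data.** Mortality, complications, readmission and length of stay are neither primary nor named secondary outcomes, and no decision rule hangs on them. This stands and limits the severity.

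**The artefact is conditional.** This stands too. The Discussion wants choice to follow wishes and needs as well as clinical reality, and narrow eligibility limits the spread in prognosis. A reader might infer that the strata will show change when nothing changed; the documents support only that they can. Nor should the strongest row of the table be read as a forecast: a correlation of 0.82 and a tripling of NOM are assumptions.

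**The undertreatment worry is a different one.** A reader might infer that a masked rise in mortality is the harm named under Strengths and limitations. That passage fears "causing undertreatment with long-term survival without functional recovery after opting for non-operative treatment", which stratum-level mortality neither measures nor hides.

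**Conclusion.** The point holds for the supporting patient outcomes. Testing before against after within NOM and operative strata conditions on a variable that the implementation is expected to move, and can produce apparent improvement in both strata or mask a real worsening. For about 30% mortality and a NOM rate going from 10% to 30%, the spurious shift in mortality is roughly -4 to -11 points (NOM) and -2 to -5 points (operated) at correlations of 0.3 to 0.8. A probit risk model gives somewhat larger shifts at the same correlation. The shift is zero if the NOM rate stays put or choice is unrelated to prognosis. These figures rest on assumed NOM rates, selection strength and risk models, and cover mortality only; the size and direction for complications, readmission and length of stay were not worked out. Describing outcomes by treatment received remains legitimate. The fault is using those strata for before-after inference. Severity: should be fixed, not critical.

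**What to change.** In Statistical analysis, replace the treatment stratification with wording to this effect:

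- Before-after comparisons of mortality, survival, complications, readmission and length of stay are made in all eligible patients regardless of treatment, adjusted for age, sex, ASA, FAC, residence, Katz ADL and fracture type.
- Strata used for inference are limited to characteristics fixed before the treatment decision, such as prefracture mobility, ADL status and fracture classification.
- Tables by NOM and operative treatment are descriptive and carry no before-after p-values.

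The cost is two or three sentences. The case-mix variables are already on the list of data taken from the audit, so no new data are needed. The definition of the NOM rate stays as it is.

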### Project timeline

Phase 1 of the study started in June 2023 and ended in August 2023. Phase 2 started in June 2023 and ended in October 2023. Phase 3 started in September 2023 and will approximately end in October 2024. Phase 4 will start in June 2024 and will approximately be concluded in June 2025.

### Patient and public involvement

A patient association representative was consulted during the drafting of the study protocol and could provide input for the study design and implementation tools. Through interviews, study participants (patients, next-of-kin and healthcare providers) will be directly involved in providing feedback on the SDM process and educational tools used during the project. In addition to general publication, a summary of the main results will be made available to study participants on request.

### Ethics and dissemination

#### Ethical approval, risks and dissemination

The study was exempted by the local Medical Research Ethics Committee (MEC-2023–0270, 10 May 2023) and Medical Ethics Committee United (W23.083, 26 April 2023) and is registered at ClinicalTrial.gov (NCT06079905, 11-10-2023). The study was approved by the board of directors of all hospitals participating in phase 3. There are no risks involved in this study. The only burden is the time needed for the interviews with healthcare providers and patients/next-of-kin in phase 3. The interviews will be performed by researchers following an opt-out design, participants can stop at any time. Participants will be asked to consent to share their contact details with the researchers and participation means interview data can be used (online supplemental materials 3). In addition, only already existing and routinely collected data will be collected. All treatments, chosen after SDM, will be performed following local standard care protocols. Based on the above, the overall burden and risks are considered negligible. The study will follow Good Clinical Practice guidelines. The study’s results will be submitted to an open access international peer-reviewed journal. As previously explained above, its protocols, tools and results will be made publicly available and presented at several national and international academic conferences of relevant orthogeriatric (scientific) associations.

10.1136/bmjopen-2023-083429.supp3Supplementary data

#### Data management, monitoring and privacy

All data and information collected regarding this study will be treated confidentially by the researchers. Research data that can be traced to individual persons can only be viewed by authorised personnel (members of the research team and members of the healthcare inspection). Data will be encoded and stored in a Castor EDC database with password-restricted access to the researchers at individual sites only. Regarding participants privacy, the Dutch ‘General data protection regulation implementation act’ will be applied.

## Discussion

### Clinical impact

This project provides an important translation of recent scientific publications to clinical practice and its success could play an important role in (inter)national surgical and geriatric guideline changes. Successful implementation of NOM will change the way healthcare providers view acute hip fractures in frail older adults with a limited life expectancy. Instead of primarily focusing on clinical possibility of hip fracture treatment, the focus will shift towards treatment concerning patients’ quality of life, harm reduction and effective palliative care in the final stages of life. Because of this shift, the NOM rate is expected to rise in this select group. However, the main goal is not to increase NOM rate but to provide each patient with the clinical care that best suits their wishes, needs and clinical reality. Nationwide implementation of SDM on NOM will also lead to a reduction of overtreatment and might reduce associated costs.^10^ Another important outcome is reduced practice variation between hospitals in both patient selection for (SDM on) NOM and nationwide implementation of a universal structured SDM protocol for frail older adults with a hip fracture.

### Strengths and limitations

The strength of this study is that it builds on an existing foundation of recent well-received (inter)national publications, countrywide initiatives involving SDM and advance care planning, and recent demands for assistance in the implementation of NOM from several hospitals. The project group includes experienced professionals from (orthopaedic) trauma surgery, geriatrics, epidemiology and implementation science from both university medical centres and general hospitals, supplemented with patient perspectives and experts in SDM and study methodology. A limitation of the project is the limited time period for the initial project. Achieving nationwide implementation within 2 years, which is the maximum allowed project duration of the grantor, might be an overoptimistic aim. However, the project will have developed a strong foundation on which future projects can build and will keep sharing its tools and information, even after completion. Another limitation is that the inclusion criteria might prove to be too narrow. There might be a larger group of patients for whom NOM could suit their preferences or goals of care. However, the project group has decided to keep strict criteria to prevent the pendulum swinging too far and causing undertreatment with long-term survival without functional recovery after opting for non-operative treatment, which results in potential decreased quality of life and associated adverse events. Depending on the results of the initial implementation, the inclusion criteria in the protocol might be adjusted to suit the needs of patients and healthcare providers. Finally, the NOM rate in the DHFA database might be an underestimation, as patients living in a nursing home might already have advance care plans preventing them from being transferred to the hospital in the case of a hip fracture. As the NOM implementation gains national traction more attention to advance care planning around hip fractures might lead to an unmeasured increase of the NOM rate in the prehospital setting. While reducing DHFA registration for this project, improved communication on patients wishes and integration of hip fractures in advance care planning, between patients and (geriatric) medical practitioners within and outside the hospital, is a desired effect that will improve the quality of NOM and patients’ treatment satisfaction.

### Future perspective

The success of this project can be used as an international example for trauma care in selected frail older adults and lead to further changes in advance care planning within this older trauma population. The projects finished protocols and clinical tools may be used for updating the Dutch national ‘Guideline for the treatment of proximal femoral fractures’ and ‘Guideline for multidisciplinary treatment of operative treatment of frail older adults’ and may also help updating international treatment guidelines on proximal femoral fractures in selected frail older adults with a limited life expectancy.
